### Interventions

Table 1 contains a summary of the details of our interventions in the format according to the revised Standards for reporting interventions in clinical trials of acupuncture (STRICTA). We will use a standardized approach to real EA (active intervention), both in terms of point selection and level of stimulation. A total of 20 needles will be used in each session. The majority of local (inner bladder meridian line in the lumbosacral area) and distal (KI-3 and 7) points will be stimulated electrically but a few points will be stimulated manually. We built in some guided flexibility in point selection, allowing the addition of up to 10 more needles to address cases where the participant reports hip/buttock pain, and/or if the participant does not experience at least 30% pain reduction after the first four sessions. Each participant cannot miss more than 3 of the 16 acupuncture sessions, to be considered as having completed treatment.

**Table 1 Tab1:** Details of treatment parameters summarized per STRICTA (version 2010) [61]

Item	Detail
1. Acupuncture rationale (explanations and examples)	1a) Style of acupuncture: - French energetics, channel theories from Chinese medicine, and neuro-anatomical (percutaneous electrical nerve stimulation (PENS)) [62]
	1b) Reasoning for treatment provided: - Point selections are based on the book by Dr J Helms, publications, and expert consensus
	1c) Extent to which treatment is varied: - We allow flexibility to include hip points if the participant reports hip/buttock pain; we also allow up to 3 additional points to be added if participants do not report at least 30% pain reduction after 4 sessions.
2. Details of needling (explanations and examples)	2a) Number of needle insertions per subject per session: - 20 (up to 30 if hip pain is present and if there is no response by the fifth session
	2b) Names (or location if no standard name) of points used: - Obligatory: GV-20, 4, BL-23, 25, 26, 28, KI-3, 7, HR-3, SI-3, BL-40 - Optional: GB-30 if there is hip/buttock pain (laterality depends on location of that pain); BL-10, 60, KI-10 if there is no response by the fifth session
	2c) Depth of insertion: - 0.5 (GV-20) to 6 cm (GB-30), depending on the location and patient size (most fall between 1 and 2 cm)
	2d) Response sought: - Deqi
	2e) Needle stimulation: - After Deqi is achieved at each needle, the following needles will also be electrically stimulated for 20–25 min: BL-23, 25, 26, 28, KI-3, 7. Then, if hip/buttock pain is present, posterior superior iliac spine (PSIS) and GB-30 - All e-stims will be bipolar, DC, at 2 Hz, and will be titrated to cause gentle muscle twitch, or to the amount that the patient can comfortably tolerate for 20 min if twitch is not obtainable
	2f) Needle retention time: 30 min
	2 g) Needle type (diameter, length, and manufacturer or material): - Auricular: Seirin J15 (0.12 × 15 mm) - Gluteal (GB-30): Huaxia (0.3 × 75 mm) - All other body needles: DBC Spring-10 (0.2 × 40 mm)
3. Treatment regimen (explanations and examples)	3a) Number of treatment sessions: 16 sessions over 8 weeks
	3b) Frequency and duration of treatment sessions: - First session up to 90 min, including the initial assessment - All subsequent sessions will be 45 min long
4. Other components of treatment (explanations and examples)	4a) Details of other interventions administered to the acupuncture - Heat lamp to low back - Auricular acupuncture to Shenmen, point zero, thalamus, and lumbar spine points
	4b) Setting and context of treatment - Participants will be informed that they may receive either real or sham EA and that both have been shown to be helpful in relieving pain
5. Practitioner background (explanations and examples)	5) Description of participating acupuncturists: 1. Licensed and ensured to administer acupuncture in the State of California 2. At least 3 years of acupuncture experience prior to treating study participants 3. Attendance at a full-day training session at the Stanford Center for Back Pain, and half-day on-site training at their own facility by the protocol co-director (JK) 4. Adequate ability to follow both the real and placebo treatment administration protocols, as assessed by the protocol co-director (JK) 5. Adequate facility to provide acupuncture treatment, approved by the protocol co-director (JK)
6. Control or comparator interventions (explanations and examples)	6a. Rationale for the control or comparator: - To minimize specific and physiologic effects, non-penetrating, Streitberger needles will be used at non-acupuncture, off-meridian points [46] - Sham electrical stimulation will be delivered via real machines with broken wires, based on a validated protocol from Wayne et al. [48] - Sham auricular points will be treated by placing a small piece of tape at the top and bottom apex of the ear - Heap lamp will be placed over the calf for approximately 20–25 min
	6b. Precise description of the control or comparator: - Point location: S1--in the middle of deltoid, 3 Cun below the lateral edge of acromion; S2--5 Cun lateral to the T-12 spinous process; S3--5 Cun lateral to L-5 spinous process; S4--midpoint on the line connecting BL-57 and GB-34 on the posterior calf - Point stimulation: minimal palpation to locate point, no Deqi. All points (S1-S4) receive sham electrical stimulation, which is performed after the acupuncturist informs the participant that he/she may or may not feel the paresthesia, because sometimes therapeutic electrical treatments are below the sensory detection threshold - The duration of needle retention and sham stimulation will be identical to that of the real treatment - Treatment regimen: same frequency and total number of treatment sessions as the real treatment in item #3, above

The sham EA (i.e., placebo intervention) has the same duration and treatment frequency as the real EA. In order to minimize specific physiological effects from the placebo EA, non-penetrating Streitberger needles will be used [46], placed at non-meridian points (away from the center of the back), which involves no electrical stimulation. The choice for placement of the needles was informed by previous research showing that even non-penetrating touch at the location of pain could lead to pain relief due to the activation of specific, non-painful, tactile c-fibers [33, 47]. We also use sham electrical stimulation in the placebo control, where the needles are connected to functioning electrical stimulators via broken wires. This particular technique was successfully used by Wane et al [48].

Initiation of new non-study pain interventions (including surgeries, pain blocks, medications, physical therapy, or chiropractic regimens) will not be allowed during the intervention period. Participants who initiate a new intervention for pain will not be included in the final analysis. To ensure patient safety, study treatments will be discontinued in the unlikely event that the participant experiences persistent, serious side effects (e.g., nerve damage). Serious side effects are rare [49] and have not occurred so far.

Fidelity: the research team will monitor acupuncturists’ treatment fidelity. A review of a random 10–15% of the sessions for each acupuncturist will be performed quarterly. We will review both the structured case report forms completed by the acupuncturists after each session and audio recordings of the sessions. To minimize the potential for drift from the treatment protocol and optimize treatment fidelity, there will be quarterly meetings of the acupuncturists and the first author, where corrective feedback of protocol deviations, if detected, will be discussed.

### Measures

#### Overview

The primary mediator is TS. The primary moderator is participants’ expectations of treatment benefits after the first treatment session. The primary clinical outcome is self-reported back pain bothersomeness. The secondary QST mediator to be examined is CPM. Secondary psychological moderators include pretreatment expectation of benefits, pain catastrophizing and self-efficacy in managing pain. Secondary clinical outcomes include the Roland Morris Disability Index, and multiple domains from the Patient Reported Outcome Measures Information System (PROMIS) item bank assessing physical and emotional functioning, fatigue and sleep. All of these assessments except for back pain bothersomeness, which is measured weekly, occur at baseline, halfway through treatment (between the 8th and 9th treatments, around the end of week 4), and post treatment (within 2 weeks after the final treatment, around week 10).

We will also collect long-term follow-up data, including back pain bothersomeness and the Roland Morris Disability Questionnaire. These will be collected at 1, 3, 6, 9, and 12 months after the end of treatment. Although not a primary aim, we collect these measures to characterize the effect of the mechanisms of interest in mediating long-term clinical outcomes.

#### Primary measures

Temporal summation (TS) - ascending pain facilitatory mechanism (primary mediator): we will use an individualized thermal TS protocol, measured on the back and the hand of each participant [50]. Through a unique participant training process and steps that aim to optimize TS by adjusting the stimulus and baseline temperatures, our method minimizes floor and ceiling effects due to variability in heat sensitivity and enables the capture of TS in a broad range of individuals [51]. This protocol delivers a series of 10 individually adjusted, supra-threshold heat pulses (0.5 s duration, given every 2 s) to the participant’s palm. TS is estimated as the difference between the rating of the second pain from the first pulse from that of the most painful pulse. We will measure TS at baseline (pretreatment measurement), during the treatment period (between the 8th and 9th treatment session), and post treatment.

Expectation of benefit - psychological mechanism (primary moderator): the Stanford Expectation of Treatment Scale (SETS) is a validated measure that assesses both positive and negative expectancies. It has a total of 6 questions (3 assessing positive and 3 negative expectations) and all questions are answered by a 7-point Likert scale scored from 1 to 7. The Cronbach’s alpha was 0.81–0.88 for positive expectancies and 0.81–0.86 for negative expectancies measured by the SETS. Participants will complete SETS both before and after the first treatment session.

Self-reported back pain bothersomeness - primary clinical outcome: participants will rate weekly back pain bothersomeness using a visual analog (VAS) 0–100 scale, where 0 is no pain and 100 is the worst pain imaginable. The back pain bothersomeness scale is specific to back pain and has been successfully used by researchers in other clinical trials [10, 52]. This measure will be collected weekly from baseline (week 0) to the post-treatment visit (around week 10).

#### Secondary measures

Conditioned pain modulation - descending pain modulation mechanism (secondary mediator): our group has optimized and published a method to quantify CPM [51]. Briefly, we measure the change in the pain rating on application of a 30-s thermal stimulus calibrated to approximately 60/100 pain intensity of the participant, applied to his/her non-dominant hand, before and during the last 30 s of a 2-min submersion of the contralateral foot in a 10 °C water bath. The magnitude of CPM is estimated as the difference in the pain rating of the thermal stimulus before and during the cold submersion. Our previous study demonstrated that CPM measured this way is robust against cognitive influences such as reappraisal or imagery [53].

Secondary psychological moderators: we will used validated questionnaires including pain catastrophizing scales [54] and self-efficacy in pain management [55].

Secondary clinical outcome measures: these will include the Roland Morris Disability Questionnaire, which assesses physical function specific to patients with back pain, and the following PROMIS measures: pain interference, physical function, social isolation, depression, anxiety, fatigue, sleep disturbance, and sleep-related Impairment. The secondary psychological moderators and clinical outcomes will be collected in a manner identical to the QST measures at baseline, at the mid-point during treatment, and post treatment.

### Timeline for participants

Figure 1 represents the participant’s timeline. Outlined in Fig. 2 (Additional file 1) is the study schedule with additional details per the SPIRIT CHECKLIST.

**Fig. 1 Fig1:**
[figure not shown]
Participant timeline. EA, electroacupuncture. Participants are randomized to verum (real) or sham acupuncture

**Fig. 2 Fig2:**
[figure not shown]
Standard protocol items: recommendation for interventional trials (SPIRIT) figure (required for study protocols). Wk, week; MINI, Mini International Neuropsychiatric Interview; QST, quantitative sensory testing; fMRI, functional magnetic resonance imaging

#### Sample size

We computed the sample size based on detecting differential changes in TS, the primary mediator. A small pilot study conducted in our laboratory suggested an average change of 10–25 points on the 100-point VAS with a standard deviation of 12 in TS following acupuncture. Prior studies suggest no treatment effect in controls receiving sham acupuncture [35]. However, given the imprecision of the pilot study estimates of effect sizes, we have elected to power the study to detect a medium-sized effect (*d* = 0.56) with 50 subjects in each arm, using the two-tailed test with alpha = 0.05 and beta = 0.8. If the point estimates from the pilot prove to be correct, this project will be very well-powered (98% power) to detect a large effect (*d* = 0.833). To account for attrition of about 20%, we plan to enroll about 120 study participants.

#### Recruitment

We will recruit participants via both online and physical venues. The online venues include social networks such as Facebook, advertising targets such as Craigslist, and research platforms such as Researchmatch.org. We also reach out to potential participants using newspaper and radio ads and flyers and brochures placed in physicians’ offices and community locations throughout the Bay Area. All interested individuals are directed to a secure, online REDCAP™ survey that functions as an initial screen for potential study participation.

#### Screening and consent

Initial eligibility will be assessed via the online REDCAP™ survey. Further eligibility will be assessed via a telephone screen based on the inclusion/exclusion criteria. Individuals who meet preliminary criteria will be scheduled for their screening visit. At the beginning of the screening visit, designated and trained research staff will review the Institutional Review Board (IRB)-approved consent and Health Insurance Portability and Accountability Act (HIPPA) forms with the participant in a private area and obtain informed consent. Research staff will allow ample time for the participant to ask questions so that the participant fully understands all the interventions and assessments associated with this study, and the benefits and risks of his/her participation. At the end of the visit, each participant will receive a signed and dated copy of their consent form and HIPPA documents.

#### Randomization, allocation concealment and blinding

We will randomize eligible participants to either the real or the sham intervention arm using a biased coin algorithm [56], which is an adaptive randomization process that aims to equalize the baseline pain level between the two groups. Given the influence of baseline pain level on clinical outcomes of pain studies [57], and our limited sample size, we decided to focus on equalizing levels of baseline pain severity, and not to equalize other factors, such as gender and age, which had less impact on the final outcome in past research [58, 59]. Each participant will be classified as having more or less extreme baseline pain (using 7/10 as a pain severity cutoff score). The algorithm will shift the randomization from a 50/50% chance of sending a participant with extreme pain into either treatment arm to having a 40/60% chance of assigning the participant with extreme pain into the arm that has more participants with extreme pain.

Participants will be randomized by the research staff who screen and enroll the participant but do not conduct baseline, mid-point, or post-treatment assessments. Specifically, once a participant is enrolled, the staff will enter the participant’s ID and pain severity into a randomization program written in R-3.4.3. The program will return the randomization assignment (i.e., allocation). A research staff member, who is not involved in the assessment of outcome, will then inform the acupuncturist via secure email, about the treatment allocation. The acupuncturist will email back, acknowledging receipt of the participant ID and allocation and will then initiate contact with the participant to schedule the first intervention session.

Blinding: both the participant and the research assistants assessing the participant will be masked (blinded) to treatment allocation. We take the following measures to ensure blinding of the participants: (1) the acupuncturists are instructed to hide all their treatment equipment from the participants before treatments; (2) participants are placed in the prone position that prevents them from seeing the intervention process; (3) we have standardized the acupuncturists’ communication with the participants so it is equal between the real and sham arms. To assess the success of these blinding measures, a blinded research assistant will administer a blinding questionnaire at the final post-treatment study visit. To ensure blinding of the research staff that assess the participants, we separate the main assessment database from the treatment database where the allocation is revealed. Additionally, the randomization staff are instructed to avoid communicating any information on treatment assignment to the assessment staff.

### Data collection methods

Plans for assessment and collection of measures: most self-report measures will be collected via electronic surveys (REDCAP™) during study visits, using an encrypted tablet connected to a secure server where the data will reside. The only exception is the weekly assessment of back pain bothersomeness, where a link to the survey will be emailed to participants. The QST data from each participant will be collected by trained research assistants at the baseline (pretreatment), mid-point (between the 8th and 9th treatment session), and post-treatment visit at our facility. All research assistants will undergo extensive training on how to administer online surveys, and more importantly, how to conduct standardized QST tests. They will watch training videos, practice on each other multiple times, then will be signed off by the first author or the manager before conducting tests on participants. Furthermore, the research assistants and the protocol directors hold weekly meetings to address issues related to data collection and standardized QST administration.

#### Strategies to encourage participant retention

We will promote adherence and retention by sending appointment reminder emails, text messages, and phone calls the day before scheduled assessment visits. In these reminders, we communicate the expectation and importance of attending all study assessment visits and not missing more than three treatment sessions. We will review the protocol timeline with each participant at the end of all visits. The team will also hold weekly meetings to troubleshoot emerging issues pertaining to retention. Finally, the participants’ compensation is also contingent on the number of assessment and treatment sessions they complete.

#### Data management

All data will be collected electronically using the HIPPA-compliant REDCAP platform. Participants will receive automated email reminders to fill out their surveys via a secure link. Some surveys and case report forms will be filled out on site, either on a desktop computer or a tablet during study assessment visits. The research team will assess data quality every 6 months by plotting data ranges and checking for missing values on the REDCAP output. These reviews will be done without unblinding. The team will also hold weekly meetings to troubleshoot emerging issues pertaining to data collection and/or participant recruitment and retention issues. The team will also hold weekly meetings to troubleshoot emerging issues pertaining to data collection.

#### Statistical methods

Given that the primary focus is on mechanisms, rather than efficacy, the primary analyses will be carried out using the per-protocol sample, consisting of participants who have completed all three assessment sessions (pre, post and midpoint), and a minimum of 13 out of the 16 treatment visits (i.e., treatment completers). Next we present analysis plan only for the primary hypotheses.

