Medications: starting new medical treatment or medication for pain 2 months prior to initiation of study procedures (participants who start such treatment after enrollment will be discontinued); opioids (≥ 60 mg morphine equivalent units/day), benzodiazepines, beta-blockers, some antipsychotics, diabetic medications, other medications that may interfere with study procedures, determined at the discretion of the study team; (selective serotonin reuptake inhibitors, anticonvulsants, and thyroid medications are not exclusionary, but tricyclic antidepressants and serotonin and norepinephrine reuptake inhibitors will be excluded); blood thinners (e.g., Coumadin, Plavix), at the discretion of the study team.

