##### Hypothesis 1a

Compared to sham, real treatment will lead to greater reduction in TS from baseline (week 0) to end of week 4.

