##### Planned analysis

This hypothesis will be tested using the two-tailed, two-sample *t* test, comparing the change in TS from baseline to week 4 between the real and sham arms.

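### Hypothesis 1a tests a week-4 outcome in a sample selected partly on attendance, visits and new pain treatment after week 4

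*Protocol article*

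**What the plan says.** The Statistical methods section defines one sample for every primary analysis: "the primary analyses will be carried out using the per-protocol sample, consisting of participants who have completed all three assessment sessions" (baseline, midpoint and post-treatment), and at least 13 of 16 treatment visits. The reason given is: "Given that the primary focus is on mechanisms, rather than efficacy".

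Hypothesis 1a reads: "Compared to sham, real treatment will lead to greater reduction in TS from baseline (week 0) to end of week 4". The planned test is a two-sided two-sample t test "comparing the change in TS from baseline to week 4 between the real and sham arms". According to the Overview under Measures, the midpoint assessment falls between the 8th and 9th sessions, and the post-treatment assessment falls within two weeks of the last session, around week 10.

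A further exclusion stands in the Interventions section: "Participants who initiate a new intervention for pain will not be included in the final analysis". The medication criterion under Participants adds that "participants who start such treatment after enrollment will be discontinued". The per-protocol definition in Statistical methods mentions neither.

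**The concern.** Hypothesis 1a is a causal comparison of randomised arms, and its outcome is fully recorded before session 9. Nothing that happens afterwards can change that outcome or the treatment received before it. Yet a participant with valid baseline and week-4 TS is removed for missing too many later sessions, missing the final visit, or starting a new pain treatment in the second half of the intervention period.

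Two things are at stake. First, selection on later events can leave groups that differ in ways randomisation had balanced. A mechanism for unequal selection is conceivable. Real treatment uses 20 penetrating needles with electrical stimulation, and more needles may be added after a poor early response. Sham uses non-penetrating needles and no current, and its description lists no such additions. Starting another pain treatment may also follow poor relief. Second, the one powered test loses participants whose endpoint is known.

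**Working it through.** **Timing**

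| Condition for entering the 1a analysis | When it is settled |
|---|---|
| Baseline and week-4 TS | By the visit between sessions 8 and 9 |
| At least 13 of 16 sessions | At most 3 missed, so at least 8 − 3 = 5 of sessions 9-16: after the endpoint |
| Post-treatment assessment | Around week 10, about 10 − 4 = 6 weeks after the endpoint |
| No new pain intervention | Throughout the intervention period, so partly after the endpoint |

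**The plan's own power.** The Sample size section gives 50 per arm, d = 0.56, two-sided alpha 0.05 and a stated 0.8, read here as power. The normal approximation is Φ(d√(n/2) − 1.96).
- d = 0.56: Φ(0.56 × 5 − 1.96) = Φ(0.84) = 80.0%. The exact t calculation gives 79.2%.
- d = 0.833: Φ(0.833 × 5 − 1.96) = Φ(2.205) = 98.6%. The exact t calculation gives 98.5%, against the stated 98%.

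Both figures reproduce. The sizing on completers is sound at d = 0.56; the issue is who is analysed.

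**How many are affected.** The plan enrols about 120. Ending with 100 completers means 20 lost (20/120 = 16.7%). Attrition of 20% means 24 lost, leaving 96, or 48 per arm. The article does not say how many of these losses come after week 4.

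**Power with all week-4 data** (exact t test, d = 0.56, 60 randomised per arm, loss before week 4 assumed):

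| Lost before week 4 | n per arm | Power |
|---|---|---|
| 20% | 48 | 77.5% |
| 10% | 54 | 82.2% |
| 5% | 57 | 84.2% |
| none | 60 | 86.0% |

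The first row equals the completer set under 20% attrition, so the gain runs from 0 to 86.0 − 77.5 = 8.5 points. For the same d, the wider set is never smaller than the completer set.

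**Possible bias when there is no true effect.** Let p be the proportion retained in an arm, r the assumed correlation between TS reduction and staying in, and z the normal point that cuts off a proportion 1 − p. The mean TS reduction among those retained shifts by r × φ(z)/p SD. The factor φ(z)/p is 0.350 at p = 0.8, 0.195 at p = 0.9 and 0.497 at p = 0.7. The SD is the pilot's 12 points. Type I error comes from 6,000 simulated trials of 60 per arm.

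| Retained, real / sham | r, real / sham | Bias in d (positive favours real) | VAS points (× 12) | Type I error |
|---|---|---|---|---|
| 80% / 80% | 0.3 / 0.3 | 0.105 − 0.105 = 0 | 0 | about 5% |
| 80% / 80% | 0.3 / 0 | 0.105 | 1.3 | about 7% |
| 80% / 80% | 0.3 / −0.3 | 0.105 + 0.105 = 0.21 | 2.5 | about 18% |
| 90% / 70% | 0.3 / 0.3 | 0.3 × (0.195 − 0.497) = −0.09 | −1.1 | about 8% |

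Swapping the arms in any row reverses the sign.

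**The case against.** The completer set is a disclosed choice with a stated reason, and it matches the sizing, which counts treatment completers. Hypothesis 1a is also the treatment-to-mediator step of 1b, so using one sample for both is coherent. The design works against unequal drop-out: participants and assessors are blinded, communication is standardised, sham has the same number and frequency of sessions, and reminders and compensation are not described as differing by arm. A new analgesic could itself alter pain ratings, which gives some reason to exclude people who start one before week 4. Those who start new treatment are to be discontinued anyway, so most would fail the completion rule.

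Much of this stands. It supports reporting a completer analysis, particularly for mediation, and it makes large bias less likely. It does not explain why attendance after session 8 should decide who counts in a contrast already measured.

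A reader might infer more than the documents support:
- That all of sessions 9-16 must be completed. At least 5 of the 8 are enough.
- That drop-out will differ by arm, or that bias must favour real treatment. The article gives no drop-out by arm or by reason. Losing only poor responders from sham would make sham look better and shrink the difference.
- That no analysis of all randomised participants will be done. The article covers only the primary hypotheses, and a separate analysis plan may add supportive analyses. The point here is the primary set, which the article fixes.

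**Conclusion.** The point holds for Hypothesis 1a. Its primary sample is conditioned on events after the endpoint is recorded, so the comparison is no longer protected by randomisation and known week-4 data are dropped. The focus on mechanisms does not justify this for a between-arm contrast.

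The size of any bias cannot be found from the documents. It is zero under equal drop-out mechanisms, and about 0.1 to 0.2 in d, in either direction, in the unequal cases with assumed correlations of 0.3. The power available from all week-4 data at d = 0.56 is 77.5% to 86%, depending on the unstated share lost before week 4.

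The argument is weaker for Hypotheses 1b and 2, whose outcome runs to week 10; there the completer set is debatable rather than plainly mistimed. The gap between the Interventions exclusion and the per-protocol definition is a matter of reconciling two sections.

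**What to change.** - **Hypothesis 1a, primary:** all randomised participants with baseline and week-4 TS, analysed in their assigned arm regardless of later attendance or later new pain treatment.
- **Missing week-4 TS:** add a sensitivity analysis, because the wider set still leaves out people lost before week 4. It reduces the selection without removing it.
- **Supportive analyses:** keep the 13-of-16 completer set and the exclusion for new pain interventions here.
- **Reconcile** the Interventions exclusion with the sample definition in Statistical methods, and separate new treatments started before the week-4 measurement from those started after it. This concerns the analysis set only, not the discontinuation rule.
- **Hypotheses 1b and 2:** report a mixed model on all available weekly scores alongside the completer analysis.

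The cost is analysis wording plus the added analyses, with no new visits, data or participants. Including less adherent participants may dilute the effect slightly, and the supportive completer analysis would help show whether it does.
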